#### Randomization and blinding

An appointed investigator who is not involved in participant recruitment, treatment, outcome assessment, or data analysis will generate the random sequence using SAS version 9.4 (SAS Institute, Inc) through a simple randomization method. The acupuncturist, who will not be involved in participant recruitment, will receive the grouping information for each participant from this investigator via short message service (SMS).

Participants in the VA and SA groups will be blinded to treatment allocation. VA and SA treatments will be performed in separate treatment rooms to reduce the risk of accidental unblinding. Participant recruitment, outcome assessment, imaging processing, and data collection, management, and analysis will be performed by independent investigators. The VA, SA, and waitlist control groups will be coded as A, B, and C, respectively, throughout the trial period until the completion of the primary analysis to ensure concealment of treatment assignment. It will be difficult to blind participants in the waitlist control group because they will not receive treatment immediately. A participant’s treatment allocation will be unblinded in the event of SAEs occurring during the trial.

The success of blinding will be evaluated for participants in the VA and SA groups at two time points (the first week and the 8th week after treatment) by asking them to guess their group allocation. The Bang’s blinding index (Bang’s BI) will be calculated according to the guessed proportion of each arm (52, 53).

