## Methods and analysis

### Study design

This is a prospective, three-armed randomized controlled trial using rs-fMRI and ^1^H-MRS, which will be jointly conducted by two hospitals in Chengdu. A total of 129 patients with ME/CFS occurring after COVID-19 and 30 HCs who have fully recovered from COVID-19 will be recruited. After baseline assessment, eligible patients will be randomly assigned to a verum acupuncture (VA), sham acupuncture (SA), or waitlist control group in a 1:1:1 ratio and will receive an 8-week intervention or wait. Figure 1 shows the flow chart of this trial. This study will be conducted in accordance with the Declaration of Helsinki, the Consolidated Standards of Reporting Trials (CONSORT) guidelines (50), and the Revised Standards for Reporting Interventions in Clinical Trials of Acupuncture (STRICTA) guidelines (51). This protocol has been reviewed and approved by the Ethics Committees of the Affiliated Hospital of Chengdu University of Traditional Chinese Medicine and the Public Health Clinical Center of Chengdu and has been registered at ClinicalTrials.gov (NCT07357688).

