### Recruitment

Participants in this study will be prospectively enrolled from COVID-19 survivors who were hospitalized at the Public Health Clinical Center of Chengdu between 01 January 2020 and 31 December 2023, as well as from outpatients of the Affiliated Hospital of Chengdu University of Traditional Chinese Medicine and community residents in Chengdu. For hospitalized COVID-19 survivors, preliminary screening will be performed by two appointed investigators through a telephone interview. Then, a face-to-face interview and routine blood tests will be performed to identify eligible participants. For other recruitment sources, advertisements will be disseminated both online and offline via platforms such as WeChat, websites, and others. The investigators will screen eligible participants according to inclusion and exclusion criteria. The written informed consent form will be obtained from each participant prior to formal inclusion.

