#### Sample size calculation

The PASS software (version 21.0.3) was used to calculate the sample size. Based on two acupuncture trials that used the Symbol Digit Modalities Test (SDMT) as the primary outcome (56, 57), we estimated that the mean and standard deviation of the change in the SDMT score at week 8 after randomization would be 3.75 ± 4.95, 2.45 ± 5.21, and 1.30 ± 4.35 for the VA, SA, and waitlist control groups, respectively. With *α* = 0.05, *β* = 0.2, a power of 0.8, and a two-sided test for group differences, 36 participants are required in each group. Assuming a 20% dropout rate, 43 cases are needed per group, resulting in a total sample size of 129 participants.

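### Simple randomisation leaves the planned 43 per arm to chance, and neither the allocation nor the primary model accounts for recruitment source

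*Protocol article*

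**What the plan says.** Under Randomization and blinding, the investigator who prepares the sequence "will generate the random sequence using SAS version 9.4 (SAS Institute, Inc) through a simple randomization method". No blocks, strata or minimisation are mentioned anywhere in the article. Study design describes assignment to verum acupuncture (VA), "sham acupuncture (SA), or waitlist control group in a 1:1:1 ratio". Sample size calculation concludes that "43 cases are needed per group, resulting in a total sample size of 129 participants".

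Recruitment names several sources. The first is survivors admitted with COVID-19 to one hospital, screened initially by telephone. Patients are also drawn from elsewhere, "as well as from outpatients of the Affiliated Hospital of Chengdu University of Traditional Chinese Medicine and community residents in Chengdu", and these are reached by advertisement.

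Under Statistical analysis, the ANCOVA for the primary outcome (change in SDMT score to week 8) adjusts for age, estimated premorbid intelligence and physical activity. Neither source nor hospital is a covariate.

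**The concern.** There are two separate issues.

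**Arm sizes.** The plan counts on equal arms but uses a method that does not produce them. Simple randomisation fixes the 1:1:1 ratio as a probability, not as a count. At stake is a little precision.

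**Recruitment source.** Patients who were admitted with acute COVID-19 could differ from outpatients and community volunteers in acute severity, and perhaps in cognition or its course. If source is related to SDMT change and falls unevenly over the arms, no term for source in the allocation or the model offsets it. At stake is a chance shift in the treatment contrasts, and some residual variance that a source term might remove.

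**Working it through.** **Inputs.** Total 129, three arms, equal probability, simple randomisation (Study design, Sample size calculation, Randomization and blinding). The share of formerly hospitalised patients is not given, so it is assumed at 10%, 20%, 33% and 50%.

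**The plan's own figure.** 36 × 1.2 = 43.2, taken as 43, and 3 × 43 = 129. This reproduces the step from 36 to 129. The 36 itself does not reproduce (see the objection below).

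**Arm sizes.** These follow a multinomial (129; 1/3, 1/3, 1/3).
- SD of one arm = √(129 × 1/3 × 2/3) = √28.67 = 5.35. The central 95% range is 33 to 54.
- Exactly 43/43/43 has probability 0.0064.
- The median of largest minus smallest arm is 10. The expected smallest arm is 37.5 and the expected largest 48.6.

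**Cost in precision.** The variance of a two-arm contrast is proportional to 1/n₁ + 1/n₂. Relative to 2/43, its average over the multinomial is 1.016, a loss of about 1.6%. The quick approximation (5.35/43)² gives 1.5%. On the protocol's assumed changes, "3.75 ± 4.95, 2.45 ± 5.21, and 1.30 ± 4.35", with root-mean-square SD √[(4.95² + 5.21² + 4.35²)/3] = 4.85, one-way ANOVA power is 53.4% at 43/43/43. Over simple-randomisation arm sizes it averages 53.0% (2.5th to 97.5th percentile 47.1% to 58.2%).

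**Source balance.** Probability that the hospitalised share differs by 15 percentage points or more (simulation, simple randomisation):

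| Assumed share | Some two arms | VA vs SA only |
|---|---|---|
| 10% | 6% | 2% |
| 20% | 20% | 8% |
| 33% | 31% | 14% |
| 50% | 35% | 17% |

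Hand check for VA vs SA at a 50% share: the SD of the difference is about √(2 × 0.5 × 0.5/43) = 0.108, and 0.15/0.108 = 1.39. The two-sided normal tail is about 16%, close to the simulated 17%.

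**Would equal arms alone help?** With arms fixed at 43 but no stratification, the 50% row gives 34% instead of 35% for some two arms. The imbalance comes from the lack of stratification, not from unequal arm sizes.

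**What a source imbalance could do.** If source shifted SDMT change by 2 points (assumed), a 15-point gap would move a contrast by 0.15 × 2 = 0.3 points. The planned VA minus SA difference is 3.75 − 2.45 = 1.30 points.

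**The case against.** The strongest reply is that nothing here is an error. Simple randomisation is unbiased, 1:1:1 holds as a probability, and no analysis in the plan needs equal arms. Because the total stays at 129, a small arm means larger others, and the average power loss is 0.4 points (53.4% to 53.0%). This stands, and for that reason the point is an improvement and not a correction of an invalid design.

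On source, every patient meets the same diagnostic and eligibility criteria and all treatment is given in one department. The outcome is a change from baseline, so stable differences in cognition largely cancel. Age, premorbid intelligence and physical activity may capture part of any source difference, and chance imbalance is already covered by the type I error. This also stands in large part. The article neither shows nor rules out a relation between source and SDMT change.

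Three stronger readings are tempting, and the document does not support them:
- A reader might infer that the trial fails if an arm falls below the stated requirement, "36 participants are required in each group", because some arm is randomised at 35 or fewer with probability 24%. That threshold carries no weight. On the protocol's own means and SDs, ANOVA needs about 77 per arm, and 36 gives 46% power. That is a separate sample size problem.
- A reader might take 35% as the risk of source imbalance. It is the highest of the assumed cases and counts any pair of arms. For VA vs SA the figure is at most 17% in the table.
- A reader might blame simple randomisation for the source imbalance. Equal, unstratified arms give almost the same figures.

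It could also be said that a journal article leaves such detail to the full protocol. Here, however, the article names the method. If a list fixed at 43 per arm is meant, the wording should be corrected.

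**Conclusion.** The point holds as a modest one. The stated method leaves the planned arm sizes to chance (SD 5.4, median gap 10) at an average variance cost of about 1.6%. Validity is not affected. Source is ignored in both allocation and primary model. A gap of 15 points or more between some two arms occurs in 6% to 35% of trials over assumed hospitalised shares of 10% to 50%, and in 2% to 17% for VA vs SA. These figures rest on the assumed mix. Whether such a gap would matter depends on how strongly source predicts SDMT change, which the document does not show. The case for changing the plan is that the better method costs very little.

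**What to change.** Replace simple randomisation with permuted blocks of randomly varying size, stratified by recruitment source (formerly hospitalised survivors versus outpatients or community residents), with block sizes withheld from recruiting staff. Include source as a factor in the ANCOVA. Blocks of 3 and 6 would keep arms within 2 of each other in each stratum, hence at most 2 + 2 = 4 apart overall. Blocking without stratification would even out the arm sizes but not the sources.

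The cost is a regenerated list, one sentence and one model term. The downside is slightly more predictable allocation, because waitlist assignment is open and part of a block can be inferred. Varying block sizes and the release of each allocation by an investigator outside recruitment limit this.

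The article does not say whether enrolment has begun. If it has, keep the existing list, describe it accurately, and add source to the model before unblinding.

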#### Statistical analysis

Statistical analysis will be conducted by an appointed statistician blinded to group allocation using R software (version 4.2.1; R Foundation). Intergroup comparisons of RSFC will be performed using the DAPBI toolbox. Normally distributed continuous variables will be reported as mean±standard deviation, while non-normally distributed data will be reported as median [P25 P75]. A *p*-value of <0.05(two-tailed) will be set as the significance level for all analyses.

The intention-to-Treat (ITT) protocol will be used for the analysis of all outcomes. The ITT population will include all participants who are randomized, regardless of treatment adherence or protocol deviations. The missing value will be handled using multiple imputations.

First, intergroup comparisons of demographic data (such as age, sex, and educational level), illness duration, estimated premorbid intelligence function, and PA will be conducted to examine comparability across the three groups. Categorical data will be analyzed using the χ^2^ test. Normally distributed continuous variables will be tested using one-way analysis of variance (ANOVA), whereas the non-normally distributed data will be analyzed using the Kruskal–Wallis test.

Analysis of covariance (ANCOVA) will be applied to the primary outcome and other cognitive measures, with age, estimated premorbid intelligence ability, and PA as covariates. ANCOVA with age and PA as covariates will be used for clinical measures and brain metabolites. Repeated measures ANOVA will be used to compare differences in hippocampal functional connectivity among the three groups. Age, sex, and years of education will be included as covariates. *Post hoc* analysis will be performed for RSFC with interaction effects. Multiple comparisons for hippocampal functional connectivity will be corrected using cluster-level family-wise error (FWE) correction, with a significance threshold set at a p-value of < 0.05. The χ2 test will be used to compare the rate of AEs and SAEs between the groups. Finally, Spearman correlation analysis will be performed to examine the relationships between cognitive outcome measures and imaging indicators exhibiting intergroup differences.

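### The protocol prints the key to its own group codes (VA = A, SA = B, waitlist = C), so the coding does not assure the stated blinding of the statistician

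*Protocol article*

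**What the plan says.** Two sections of the protocol article bear on this.

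- **Randomization and blinding.** The arms are given letters: "The VA, SA, and waitlist control groups will be coded as A, B, and C, respectively". The same sentence sets the period and the purpose: the letters apply "throughout the trial period until the completion of the primary analysis to ensure concealment of treatment assignment". This section also separates roles, so that "data collection, management, and analysis will be performed by independent investigators", and it has the random sequence generated by an investigator who takes no part in recruitment, treatment, outcome assessment or analysis.
- **Statistical analysis.** "Statistical analysis will be conducted by an appointed statistician blinded to group allocation".

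Nowhere does the article say that the analysis dataset carries other labels, that the letters will be reassigned, or that their meaning is kept from the analyst.

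**The concern.** A code conceals only while its key is withheld. Here the sentence that creates the code also supplies the key, in a published document that the statistician has to work from. The coding therefore cannot do the job the protocol gives it, and the later statement that the statistician is blinded loses the only labelling safeguard described for it.

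At stake is protection against analysis choices being made, even unintentionally, with knowledge of the arm. This matters most for verum against sham acupuncture. The Discussion presents that contrast as the one that isolates the specific effect of acupuncture, and those two arms would otherwise be hard to tell apart in a dataset. The trial would also report a blinded statistician on the strength of a procedure that does not secure it.

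**Working it through.** The protocol gives no figure to reproduce and no formula applies. The check sets the statements side by side.

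1. **The key.** The wording assigns the letters in order, so A is verum acupuncture (VA), B is sham acupuncture (SA) and C is waitlist. The assignment is fixed and public.
2. **The purpose.** The letters are meant to conceal assignment until the primary analysis is complete. They must therefore hold during exactly the period in which the statistician works with the data.
3. **The claim that depends on it.** The statistical analysis section declares the statistician blinded to allocation. To run the specified analysis (ANCOVA with the named covariates for the primary outcome), the statistician needs the protocol and a dataset with a group variable.
4. **Combining these.** A group variable coded A, B or C, read with the published mapping, identifies the arm of every participant in that dataset. No further information is needed.
5. **Search for a remedy elsewhere in the article.** Role separation means that different people do different tasks; it does not hide what a letter stands for. Keeping sequence generation apart from analysis protects the list, not the label. Nothing else in the article addresses the point.
6. **How much random letters could protect.** Allocation guesses, used for Bang's blinding index, are collected only from the VA and SA groups. If those responses are in the dataset, the arm without them is the waitlist, whatever its label. What a sound code would preserve is mainly the distinction between VA and SA. At the planned 43 per group that is 43 + 43 = 86 of 129 patients, or two thirds. Because the protocol specifies simple randomization, the realised number may differ.

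**The case against.** The strongest case on the other side has four parts.

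- **Declared blinding.** The protocol states that the statistician is blinded, and nothing shows that the key was or will be used. This stands. A reader might infer that the statistician is in fact unblinded; the documents support only that the described procedure does not assure blinding.
- **Other safeguards.** Independent sequence generation, separated roles and, for participants, the sham device and separate treatment rooms do not depend on the letters. This also stands. The point does not touch the blinding of VA and SA participants.
- **Little left to discretion.** A reader might infer that many analytic choices would be made by people who know the arm. The article does not bear this out for the obvious candidates. Spectral quality has numeric limits for signal-to-noise ratio, line width and Cramer–Rao bound. Head-motion exclusion is fixed at more than 3 mm or 3°. The choice between ANOVA and Kruskal–Wallis belongs to the baseline comparability step, while the primary outcome is assigned ANCOVA. The imputation model, and which of the physical activity summaries serves as covariate, are not named in the article. A statistical analysis plan commonly settles such matters, so they cannot be counted as open. Nor does the article say that image processors receive the group label, and preprocessing is done participant by participant.
- **A condensed article.** A fuller protocol or analysis plan could describe further safeguards. That is true of omitted detail, but this is a positive statement that defeats its own purpose. A fuller document could introduce different labels; it could not make this published mapping secret.

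These arguments limit the consequences. They leave the core point intact.

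**Conclusion.** The point holds in a limited form. The published mapping of letters to arms defeats the concealment it is meant to provide, so the coding does not assure the blinding that the statistical analysis section declares. The exposure is shown for anyone who holds letter-coded data and the protocol, chiefly the statistician.

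The practical loss lies mainly in VA versus SA, about 86 of the 129 patients at the planned allocation. The size of any resulting bias cannot be computed from the documents, and they do not show that any result is or will be compromised. The conclusion assumes that the analysis dataset carries the letters as the protocol describes and that no document outside the article replaces them. The sponsor should correct this before the analysis dataset is prepared.

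**What to change.** - Have the investigator who generates the random sequence, and who takes no part in the analysis, assign new neutral labels to the three arms at random for the analysis dataset.
- Withhold the key from the statistician until the primary analysis is locked, then release it.
- Replace the fixed A/B/C mapping in the section on randomization and blinding with a description of this procedure. Deleting the mapping alone would restore nothing, because it is already published; the labels themselves have to change.

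The cost is one relabelling of the dataset and an amendment to one sentence. Sample size, outcomes, the analysis model and trial conduct are unaffected. Where the allocation guesses are part of the dataset, the new labels will protect VA versus SA but may not hide the waitlist arm, and the amended text should not claim more than that.

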#### Interventions

Healthy controls (HCs) will not receive any intervention during the trial period; clinical and brain imaging data will be collected only once. All interventions will be carried out in the outpatient department of the Affiliated Hospital of Chengdu University of Traditional Chinese Medicine. A trained and certified acupuncturist with at least 5 years of working experience will administer the interventions. The treatment protocol consists of 24 sessions, each lasting 30 min, administered over 8 weeks (three sessions per week). The acupuncturist will twirl and lift or thrust needles for 10 s every 15 min during each treatment session. The acupuncturist is not allowed to discuss the effects of acupuncture with the participants during the treatment period.

##### Verum acupuncture group (VA)

According to analyses of acupoint selection in acupuncture treatment for ME/CFS (54) and MCI (55), two sets of acupoints have been selected for the VA group. The first set includes Baihui (GV20), bilateral Shenmen (HT7), bilateral Neiguan (PC6), Qihai (CV6), Guanyuan (CV4), bilateral Zusanli (ST36), and bilateral Sanyinjiao (SP6). The second set consists of Sishenchong (EX-HN1), bilateral Ganshu (BL18), bilateral Pishu (BL20), bilateral Shenshu (BL23), and bilateral Taixi (KI3). One set of acupoints will be used in each treatment session, and the two sets of acupoints will be applied alternately. The locations of the acupoints conform to the 2021 National Standards of the People’s Republic of China (GB/T12346–2021) and are presented in Table 1.

**Table 1 tab1:** Locations and needling methods of acupoints used in the verum acupuncture group.

Acupoints	Locations	Needling methods
Baihui (GV20)	On the top of the head, 5 cun above the midpoint of the anterior hairline.	Subcutaneous insertion 0.5–0.8 cun; twirling the needle to elicit Deqi sensation.
Shenmen (HT7)	On the inner area of the wrist, at the ulnar end of the distal wrist crease, in the depression along the radial side of the flexor carpi ulnaris tendon.	Perpendicular insertion 0.3–0.5 cun; twirling or lifting and thrusting the needles to elicit Deqi sensation.
Neiguan (PC6)	On the inner area of the forearm, 2 cun above the distal wrist crease, between the palmaris tendon and the radial wrist flexor tendon.	Perpendicular insertion 0.5–1 cun; twirling or lifting and thrusting the needles to elicit Deqi sensation.
Qihai (CV6)	On the lower abdominal area, 1.5 cun below the navel, on the anterior midline.	Perpendicular insertion 1–1.5 cun; twirling or lifting and thrusting the needles to elicit Deqi sensation.
Guanyuan (CV4).	On the lower abdominal area, 3 cun below the navel, on the anterior midline.	Perpendicular insertion 1–1.5 cun; twirling or lifting and thrusting the needles to elicit Deqi sensation.
Zusanli (ST36)	On the outer side of the lower leg, 3 cun below the outer knee point and one finger-breadth lateral to the anterior border of the tibia.	Perpendicular insertion 1–2 cun; twirling or lifting and thrusting the needles to elicit Deqi sensation.
Sanyinjiao (SP6)	On the medial side of the shank, 3 cun above the tip of the medial malleolus, along the posterior medial edge of the tibia.	Perpendicular insertion 1–1.5 cun; twirling or lifting and thrusting the needles to elicit Deqi sensation.
Sishenchong (EX-HN1)	On the top of the head, 1 cun lateral to Baihui (GV20) in the anterior, posterior, left, and right directions; a total of 4 points.	Subcutaneous insertion 0.5–0.8 cun; twirling the needles to elicit Deqi sensation.
Ganshu (BL18)	On the back, below the spinous process of the 9th thoracic vertebra, 1.5 cun away from the posterior midline.	Oblique insertion 0.5–0.8 cun toward the spine; twirling the needles to elicit Deqi sensation.
Pishu (BL20)	On the back, below the spinous process of the 11th thoracic vertebra, 1.5 cun away from the posterior midline.	Oblique insertion 0.5–0.8 cun toward the spine; twirling the needles to elicit Deqi sensation.
Shenshu (BL23)	On the lower back, below the spinous process of the 2nd lumbar vertebra, 1.5 cun away from the posterior midline.	Perpendicular insertion 0.5–1 cun; twirling or lifting and thrusting the needles to elicit Deqi sensation.
Taixi (KI3)	The inner side of the ankle, in the depression between the tip of the medial malleolus and the tendo calcaneus.	Perpendicular insertion 0.5–1 cun; twirling or lifting and thrusting the needles to elicit Deqi sensation.

Participants will lie in a supine or prone position while receiving VA treatment. Disposable sterile acupuncture needles (0.30 mm × 40 mm or 0.30 mm × 0.25 mm, Hwato brand, Suzhou Medical Supplies Factory Co., LTD., Suzhou, China) will be used for the treatment. The needling method for each acupoint is shown in Table 1.

